### Study sample and setting

2.2

The study is conducted as a multicenter-study in three day clinics for children and adolescent psychiatry in northern Germany. Participating clinics comprise of the day clinic facility of the Clinic for Child and Adolescent Psychiatry, Psychotherapy and Psychosomatics at the Center for Integrative Psychiatry, School of Medicine in Kiel and the two day clinics of the Department for Child and Adolescent Psychiatry and Neurology at the Rostock University Medical Center in Rostock. All patients and parents/custodians receive age-appropriate information about the study procedure and the collection of data. The collection of study data is only possible if written informed consent is granted by both, children and parents/custodians. Depending on the facility, groups consist of different age ranges overall ranging from 10 to 18 years. Age-related differences regarding time needed to fill out questionnaires and worksheets are accounted for by personnel to ensure the programs practicability across all age groups. Groups may vary in size depending current treatment capacity. Inclusion criteria for this study are rather limited: To take part in the study the patients need to be between 10 and 18 years old, being treated in the facility consistently for the whole duration of the study and need to be able to comprehend presented concepts such as time. Further a sufficient understanding of the German language as well as the ability to read and write short phrases is required. Patients that do not consent to their data being processed take part in the intervention nevertheless. They fill out the questionnaires and sleep logs relevant to the intervention, but those will not be collected for analysis and no actigraphy will be recorded.

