### Study design

2.1

The study is conducted using a waitlist-control-design. Each participant attends three sessions in a group therapy setting, with session T0 and T1 forming the primary focus to detect a treatment effect (Figure 1). The third timepoint, T2, serves for further exploratory analysis and to deliver the intervention to the control group as well. Two out of three sessions are the RfL-sessions, while a third one is of an unrelated topic. Participants are quasi-randomized into intervention or control group. Allocation of participants to the group is based on the time they begin treatment in the facility. Whether the participants belong to the control or intervention group is determined by the alternating nature of their occurrence. After an intervention group lasting 28 days an about 8–10 weeks pause interval follows to reach a sufficient amount of new, naive-to-the treatment admissions. After that a control group of 28 days starts, also followed by an 8–10 weeks pause interval afterwards. This process, alternating between intervention and control group with an 8–10 weeks pause interval in between, is continued until the required number of participants has been reached. Participation from start to end lasts 28 days representing 4 weeks around the described timepoints. The measurements collected for this study consist of different self-report questionnaires, sleep logs and actigraphy data. Psychometric properties of the questionnaires used are described below.

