The intervention consists of two 90-min sessions held 1 week apart from each other. In the intervention group those sessions take place at T0 and T1, the control group undergoes the intervention at T1 and T2. To give patients as much control as possible over their sleep routine, the intervention is implemented in day-clinic treatment settings for children and adolescents in psychiatric care. During the first session, patients learn about the functionality of healthy sleep, reflect on their own current sleep quality, sleep habits, and sleep hygiene and are introduced to the airplane metaphor. The metaphor explains sleep hygiene as a well-structured and segmented process consisting of different phases which enable pilots to land the plane safely, in other words to establish a good routine to go to sleep and is depicted in Figure 2. The landing of a passenger airplane is described to pass through 12 stages which are grouped into four phases: flight schedule, descent, landing approach and park position. In the “flight schedule” phase, consistent times for departure, as well as preparations regarding the takeoff and the flight itself are outlined. During “descent” service of food and beverages is stopped and passengers must remain seated. The patients are further advised not to take naps 3 h before bedtime. According to the common sleep hygiene recommendations it is emphasized not to nap after 3 p.m. The difficulty, however, was that the day clinic treatment was not finished until around three o’clock. In order to address this important rule, therefore the time window had to be adjusted accordingly (no nap 3 h before bedtime). Although the time stated on the poster may seem too late, it was pointed out during training that it was important not to nap too late and certainly not 3 h before bedtime.” During the third phase, the “landing approach,” electronic devices have to be turned off (“flight mode”), passengers are told to sit back and relax and in case of turbulences or obstructions on the runway a loop is flown and landing is restarted shortly after. The fourth phase mainly targets the processes occurring when the plane landed and is pulled into its hangar. It is therefore named “Take park position” and describes the importance of a clean and functional but also welcoming hangar which is used for this purpose only. Each phase corresponds to a specific time window. The first phase mainly describes the day starting with getting up and ending with the time to start preparing for bedtime. The second phase, “descent,” covers 3 h before bedtime while the third phase, “landing approach,” comprises of the last 30 min before the planned bedtime. Phase four, “Take park position,” mainly consist of the night and daytime preparations making sure the sleeping place is ready when it needs to be.

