### Eligibility criteria

2.3

There is no specific group of patients with specified disorders targeted in this study since we aim to improve sleep problems across different psychiatric disorders. Participants will be included in the study if they are patients of day clinic facilities of clinics of child-and adolescent psychiatry at the age of 10–18 years old, have sufficient German language skills and gave their written informed consent. Patients at the age under 18 years old will be included if both the patient and legal guardians consented. Participants will be excluded from the study if they leave the inpatient facility before the second intervention session.

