### Sample size calculation

2.4

The sample size was computed assuming a repeated measures ANOVA with a within-between interaction using g*Power 3.1 (Faul et al., 2009) with the sleep duration used as primary outcome measure. We assumed a middle effect size (*d* = 0.25), a power of 0.90 and an alpha-error of 5%. This resulted in a minimum sample size of *N* = 46 participants. As we expect a drop-out rate of about 25%, the target enrollment is 60 participants.

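### Sections 2.2 and 2.3 give eligibility lists that do not match, and the full-stay condition in 2.2 does not say whether planned or actual stay is meant

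*Protocol article*

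**What the plan says.** Section 2.2 (Study sample and setting) introduces its list as inclusion criteria. Besides age 10 to 18, it requires "being treated in the facility consistently for the whole duration of the study". Patients also "need to be able to comprehend presented concepts such as time". Sufficient German is needed, and "the ability to read and write short phrases is required".

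Section 2.3 (Eligibility criteria) restates eligibility. Participants are day-clinic patients aged 10 to 18 who "have sufficient German language skills and gave their written informed consent", with guardian consent for those under 18. It names no length of stay and no comprehension of time. Its one exclusion is: "Participants will be excluded from the study if they leave the inpatient facility before the second intervention session".

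The timing is set elsewhere. Section 2.1: "Participation from start to end lasts 28 days representing 4 weeks around the described timepoints". Section 2.1.1 places the two sessions one week apart: "In the intervention group those sessions take place at T0 and T1, the control group undergoes the intervention at T1 and T2". Sections 2.1 and 2.9 make T0 versus T1 the primary comparison. T2 serves exploratory analysis and brings the intervention to the control group. Section 2.4 expects about 25% drop-out.

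**The concern.** Two adjacent sections state who is eligible, and they differ on two conditions. On comprehension of time, one list is simply longer than the other. The stay condition is the more serious difference, because the two sections place the decisive moment at different times: the end of the 28 days in 2.2, the second intervention session in 2.3.

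If 2.2 is applied as written, a participant's eligibility is settled by what happens after T1. That is a completer restriction in the form of an entry criterion. Early discharge or transfer may well be related to improvement or deterioration. The article itself links sleep quality to symptom severity at discharge (Discussion) and mentions the high turnover of patients (Limitations). Removing such patients after the primary outcome has been measured could bias the T0–T1 comparison, and patients and staff are not blind to condition (section 2.6). With three day clinics, the rule needs one meaning.

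**Working it through.** **1. The two lists side by side**

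| Condition | Section 2.2 | Section 2.3 |
|---|---|---|
| Age 10–18 | yes | yes |
| Sufficient German | yes | yes |
| Reading and writing short phrases | yes | not named; may be covered by German skills |
| Comprehension of time | yes | no |
| Treated for the whole study | yes | no |
| Leaves before second intervention session | not named | excluded |
| Consent | yes, as a condition for collecting data | yes |

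No other section reconciles the two stay rules.

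**2. Timing.** The sessions at T0 and T1 are one week apart in the intervention group, and those at T1 and T2 are one week apart in the control group. I assume that the three sessions sit centrally in the 28 days, so T0, T1 and T2 fall at about days 7, 14 and 21. The article does not give the days.

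**3. Test cases, reading 2.2 literally**

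- Either arm, leaves on day 24 after all three sessions: fails 2.2, not excluded by 2.3.
- Intervention group, leaves between T1 and T2: fails 2.2, not excluded by 2.3, because the second session was T1.
- Control group, leaves between T1 and T2: fails 2.2 and is also excluded by 2.3, because the second session is T2.

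**4. The plan's own figures.** With an effect size f = 0.25 (printed as d), two groups, two timepoints, alpha 0.05 and an assumed correlation of 0.5, the within-between interaction has λ = f²·N·m/(1 − ρ) = 0.0625 × 46 × 2/0.5 = 11.5 on 1 and 44 degrees of freedom. Power is 0.912, and N = 44 gives 0.8997, so N = 46 is reproduced. The article gives no correlation; N would be 62 at 0.3 and 28 at 0.7. For drop-out, 46/0.75 = 61.3, so 62 against the stated 60. Conversely, 60 × 0.75 = 45 remain, with power 0.906 at correlation 0.5. If the 25% already covers everyone who leaves within 28 days, the stay rule costs no power beyond what was budgeted. The issue is selection.

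**5. How many would fail 2.2 and pass 2.3.** Assumptions: 30 per arm, 25% leave, departures spread evenly over 28 days, T1 at day 14, T2 at day 21.

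- Intervention, leaving after T1: 30 × 0.25 × 14/28 = 3.75
- Control, leaving after T2: 30 × 0.25 × 7/28 = 1.875
- Total: 3.75 + 1.875 = 5.625, about 5–6 of 60 (5.625/60 = 9.4%)

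The result depends on when patients leave. If all the 25% is lost before T1, the number is 0. If all of it is lost after T2, it is 60 × 0.25 = 15.

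**The case against.** The best defence is that the lists are cumulative. Neither claims to be exhaustive, so a patient must satisfy both, and someone who cannot handle time is ineligible under 2.2. This stands for comprehension of time. Literacy may be covered by sufficient German, and the word inpatient in 2.3 is a slip, since the same paragraph speaks of day clinics.

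For the stay condition, the defence is that 2.2 describes what is needed to take part, so planned stay is meant, and 2.3 then says what happens when someone leaves. This is plausible. If the actual stay were required, the second-session exclusion would be redundant, because anyone who leaves before that session already fails 2.2. But the text states the condition without any word such as planned or expected, so the reading has to be supplied.

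A reader might go further than the document allows in four ways:

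- **That the stay rule can only be judged after the outcome.** This is true only of the literal reading.
- **That it cannot be squared with 25% drop-out.** Under planned stay the two fit together, and drop-out may also include withdrawn consent or missing recordings.
- **That 7–8 of 60 are affected.** 60 × 0.25 × 14/28 = 7.5 counts everyone who leaves after T1, including the 1.875 controls who leave before T2 and so fail 2.3 as well.
- **That all of these patients have complete primary data.** This is shown only for the PSQI, which is filled in at the start of each session (section 2.1.2). Actigraphy sleep time is also primary (section 2.7), and the article does not say which nights represent T1.

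Nor does the article say that patients who leave after T1 will be dropped from the analysis. Analysis populations may be defined in an analysis plan that is not shown. The objection here is to eligibility as printed.

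**Conclusion.** The mismatch is real and unresolved in the article. Its consequential part is the stay condition: a patient who completes the sessions but leaves before day 28 fails 2.2 as written and is not excluded by 2.3. On the literal reading, 2.2 is a post-baseline selection rule that acts after the T0–T1 comparison. On the planned-stay reading, it is an ordinary entry criterion that is badly worded. The document does not show that sites will enrol different populations or that outcome-related selection will occur; it leaves room for both.

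The size cannot be derived from the article. About 5–6 of 60 is an illustration that rests on even departures, assumed session days and equal arms, within a range of 0 to 15 as departures move from before T1 to after T2. This merits a correction because the correction is cheap and removes the possibility of selecting participants after their primary outcome is known.

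**What to change.** Merge sections 2.2 and 2.3 into one list, judged once at or before T0: age 10 to 18, day-clinic patient, sufficient German including reading and writing short phrases, comprehension of time, and consent. Reword the stay condition as expected, at T0, to remain in treatment for the planned study period. Expected stay through T1 alone would be too short, because it would admit controls not expected to reach their second session at T2.

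State that actual early departure is drop-out and not ineligibility. Participants who leave after T1 stay in the T0–T1 analysis in both arms with whatever T0–T1 data they have. Reconcile the second-session exclusion in 2.3 with this. As printed, it still removes controls who leave between T1 and T2 and keeps intervention patients who leave in the same interval. Correct inpatient to day clinic.

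The cost is a wording amendment, with no extra patients or measurements. Some participants will lack T2 data or late actigraphy, and some controls will leave before completing the intervention; both should be reported.

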### Eligibility criteria

2.3

There is no specific group of patients with specified disorders targeted in this study since we aim to improve sleep problems across different psychiatric disorders. Participants will be included in the study if they are patients of day clinic facilities of clinics of child-and adolescent psychiatry at the age of 10–18 years old, have sufficient German language skills and gave their written informed consent. Patients at the age under 18 years old will be included if both the patient and legal guardians consented. Participants will be excluded from the study if they leave the inpatient facility before the second intervention session.

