#### Questionnaires and actigraphy

2.1.2

The study aims to detect improvement in subjective and objective domains of sleep following the intervention. Subjective sleep quality is assessed using PSQI (Buysse et al., 1989). The PSQI consists of 24 items covering seven domains of sleep quality including sleep quality, sleep latency, sleep duration, sleep efficiency, sleep disturbances, use of medication, and daytime sleepiness. The PSQI is a validated and widely used self-report measure for sleep quality showing good reliability, internal consistency, criterion validity and discriminatory power. A global score of five has been deemed sufficient to discriminate between good and bad sleep quality (Buysse et al., 1989). Those findings have been replicated for the use of the PSQI in minors (La Vega et al., 2015; Larche et al., 2021). To assess daytime sleepiness, we use the Epworth Sleepiness Scale for Children and Adolescents (ESS-CHAD, Janssen et al., 2017) which consists of eight items regarding the tendency to fall asleep during different age-adjusted daytime activities such as during lessons in school. The ESS-CHAD has been shown to be a reliable and valid measure to assess daytime sleepiness in minors (Janssen et al., 2017). Both questionnaires were chosen because they are applicable to our wide age range from 10 to 18 years of age likewise and are commonly used in sleep research. This ensures comparability within the group of participants and also allows to compare our results to those of other researchers. PSQI and ESS-CHAD are distributed at the beginning of every session so that the participants answer them before they receive any new elements of the intervention during the sessions. They are instructed to focus on symptoms present in the last week. Between sessions the patients keep a sleep log that monitors aspects such as bedtime, waketime, total sleep duration, duration until they fall asleep and subjective aspects such as perceived rest-and wakefulness each day during the week. Those subjective measures will be complemented by actigraph data to gain insides about possible incremental validity. The comparability of subjective and objective sleep data collected in this study will be subject of another study. Hence, this will be described in an additional study protocol, which aims to gain insight on subjective and objective measurements of sleep in youth with mental health problems.

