### Data analysis

2.9

The study is conducted using a control design in which the control group receives regular group therapy. To detect treatment effects, variance in between intervention and control group at T0 and T1 (see Figure 1) is assessed by using a repeated measures ANOVA including two factors (GROUP and TIMEPOINT). Significance level is set to be at *p* = 0.05. Post-hoc tests will clarify effect size and direction. If statistical assumptions are not met, non-parametric alternatives will be used. In additional exploratory analyses we plan to account for sociodemographic aspects or the influence of different diagnoses for the efficacy of the program.

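### The exclusion for early leavers runs to T1 in the intervention arm but to T2 in the control arm, although the primary comparison ends at T1

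*Protocol article*

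**What the plan says.** Four statements in the protocol article bear on this.

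- Exclusion (Eligibility criteria, 2.3): "Participants will be excluded from the study if they leave the inpatient facility before the second intervention session".
- Schedule (section 2.1.1, on the intervention): "In the intervention group those sessions take place at T0 and T1, the control group undergoes the intervention at T1 and T2". The spacing is also fixed: "The intervention consists of two 90-min sessions held 1 week apart from each other".
- Analysis (Data analysis, 2.9): "variance in between intervention and control group at T0 and T1 (see Figure 1) is assessed by using a repeated measures ANOVA". The Study design section gives the last timepoint a different role: "The third timepoint, T2, serves for further exploratory analysis and to deliver the intervention to the control group as well".
- A second stay rule (Study sample and setting, 2.2): the inclusion criteria require "being treated in the facility consistently for the whole duration of the study". Participation lasts 28 days according to Study design.

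On data collection, the section on questionnaires and actigraphy says "PSQI and ESS-CHAD are distributed at the beginning of every session". The Limitations section confirms that controls fill in the T1 questionnaires before they receive any of the intervention.

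**The concern.** An exclusion tied to the second intervention session follows each arm's own schedule, and the schedules are shifted by a week. Controls must therefore remain one week longer than intervention patients to count, and that week lies after the primary comparison is over. Patients who leave a psychiatric day clinic may have improved, worsened or disengaged. The document gives no data on this, but departures unrelated to sleep cannot be taken for granted. Controls who leave after T1 have also just had their first intervention session.

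At stake is the comparability of the arms at T1 in a small, unblinded trial whose arms are formed by alternating time blocks. The rule would also throw away primary-outcome data already collected.

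**Working it through.** **Step 1: map the rule onto the schedule.**

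| | Intervention | Control |
|---|---|---|
| First intervention session | T0 | T1 |
| Second intervention session, where exclusion ends | T1 | T2 |
| Last timepoint in the primary comparison | T1 | T1 |
| Leaves between T1 and T2 | kept | excluded |
| PSQI at T0 and T1 available for that patient | yes | yes |

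The PSQI row is explicit, because the questionnaire is completed at the start of each session. For actigraphy the protocol does not define which nights make up the T0 and T1 values. Complete sleep-duration data by T1 is probable but inferred.

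**Step 2: reproduce the plan's sample size.** Inputs from section 2.4: effect size 0.25, power 0.90, alpha 0.05, N = 46, drop-out about 25%, target 60. Assumption: correlation ρ = 0.5 between timepoints. For the within-between interaction with 2 groups and m = 2 timepoints, λ = N·f²·m/(1−ρ). With f = 0.25 and N = 46, λ = 46 × 0.0625 × 2/0.5 = 11.5 and power is 0.912; N = 44 gives 0.8997. So N = 46 reproduces with 0.25 read as Cohen's f. Then 46/0.75 = 61.3, close to the stated 60.

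On the scale of a two-arm comparison of change, λ = (N/4)·δ². Setting this equal to 0.25·N gives δ = 1.0 SD of change.

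**Step 3: illustrate the size.** No weekly departure rate is given. Assumptions: 30 per arm, the same constant rate in both arms, and a fraction q leaving over w weeks. The fraction still present after t weeks is S(t) = (1−q)^(t/w). Counting from T0, T1 is t = 1 and T2 is t = 2. Controls discarded after T1 = 30 × [S(T1) − S(T2)].

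Worked case, q = 0.25 and w = 4: S(1) = 0.75^(1/4) = 0.931, S(2) = 0.75^(1/2) = 0.866, and 30 × (0.931 − 0.866) ≈ 1.9.

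Power uses f = 0.25, ρ = 0.5 and, for unequal arms n₁ and n₂, an effective N of 4n₁n₂/(n₁+n₂).

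| Departure rate | Counted from | Excluded, intervention | Excluded, control | Controls discarded after T1 | Power: rule / common T1 cut-off |
|---|---|---|---|---|---|
| 25% per 4 weeks | T0 | 6.9% | 13.4% | 1.9 | 0.949 / 0.956 |
| 25% per 4 weeks | 1 week before T0 | 13.4% | 19.4% | 1.8 | 0.934 / 0.942 |
| 25% per 2 weeks | T0 | 13.4% | 25.0% | 3.5 | 0.925 / 0.942 |
| 25% per 2 weeks | 1 week before T0 | 25.0% | 35.0% | 3.0 | 0.884 / 0.906 |
| 10% per 4 weeks | T0 | 2.6% | 5.1% | 0.8 | 0.962 / 0.964 |
| 10% per 4 weeks | 1 week before T0 | 5.1% | 7.6% | 0.7 | 0.957 / 0.960 |

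Between 0.7 and 3.5 of 30 controls are discarded. The power difference is 0.2 to 2.2 points.

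**Step 4: what if the whole-duration rule is the operative one?** It is worded the same for both arms. With 25% leaving over the 28 days counted from T0, it would discard 30 × (0.931 − 0.750) ≈ 5.4 patients per arm who were present at T1. It removes the difference between arms in the rule, but loses more primary data.

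**The case against.** The strongest reply is that the whole-duration criterion applies equally to both arms. If it governs, an intervention patient who leaves between T1 and T2 fails it too, and the asymmetry disappears. This stands in part: selection that differs by arm follows only where the section 2.3 exclusion is the rule actually applied. But the criterion does not rescue the plan. Whether a patient will stay cannot be known at entry, enforcing it would make the section 2.3 rule redundant, and it would still select on events after allocation. The two rules do not combine into one coherent instruction.

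A second reply is that the second intervention session might mean the second session of any kind, hence T1 for everyone. Study design and the Figure 1 caption speak against this, since controls begin with group therapy unrelated to the intervention. If T1 was meant, the sentence still needs correcting.

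Third, analysis sets are often left to a SAP, which is not shown. That would excuse silence, but here the protocol states a rule.

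Two stronger readings are tempting and not supported:

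- A reader might infer that every discarded control has complete primary data. That is explicit for the PSQI only. Actigraphy sleep duration is also primary, and its T0 and T1 windows are undefined.
- A reader might assume that leavers differ from stayers by 0.5 to 1.0 SD in change, obtain a shift of 0.069 × 0.5 to 0.069 × 1.0, about 0.03 to 0.07 SD, and set it against the stated 0.25 as up to 28% of the effect. The scale is wrong: 0.25 reproduces the sample size as f, equivalent to 1.0 SD of change, so the same shift is about 3% to 7% of the effect powered for. The assumed 0.5 to 1.0 SD has no source in the document either.

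**Conclusion.** The point holds as a defect in a stated rule. Sections 2.1.1 and 2.3 together end the exclusion window one week later in the control arm, beyond the last timepoint of the primary comparison, and section 2.2 adds a conflicting stay requirement.

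The number affected is probably small: about 1 to 4 of 30 controls if 10% to 25% leave at a constant rate that is equal in both arms. All of these are assumptions. The cost in power is minor. What matters is selection on a post-allocation event that differs by arm, and neither its direction nor its size can be derived from the document. It should be corrected before analysis, but it is not of the weight that would by itself undermine the trial. Allocation by alternating calendar blocks, with the seasonal and holiday confounding the authors acknowledge, is a larger threat to comparability.

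**What to change.** 1. Reconcile sections 2.2 and 2.3 so that one statement governs how departures are handled.
2. Define the primary analysis set identically in both arms: all allocated participants with a T0 assessment, analysed by allocated condition, using all available T1 data whatever happens after T1.
3. Word the section 2.2 criterion as expected stay for the study period, judged at enrolment.
4. If an attendance-based set is wanted, anchor it at T1 in both arms and use it only as a sensitivity analysis.

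This means rewording two sentences and adding one on the analysis set. It requires no further patients or measurements and retains data already collected. Stating which nights form the T0 and T1 actigraphy values would settle whether the T1 cut-off is also sufficient for sleep duration.
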